### Randomization

Randomization will occur following pre-assessment. This will be conducted by an independent research assistant located off-site (University of New South Wales) and not involved in any other aspects of the study. Randomization will be performed using computerized software on a 1:1 basis.

### The Problem Management Plus (PM+) program

The WHO PM+ program involves a set of a brief psychological strategies that seek to ameliorate symptoms of common mental health problems (e.g. depression, anxiety, stress). The intervention protocol was written for WHO by a consultant of the University of New South Wales, Australia [12, 16].

The PM+ intervention protocol has been translated into Kiswahili and adapted to the local sociocultural context of the lives of women in poor neighborhoods of Nairobi. The translation and adaptation have been reviewed in two workshops: one with experts on the intervention and the other with community representatives including local leaders, local health care provides, community health workers (CHWs) and Kenyan translators [17].

PM+ integrates problem-solving and behavioral treatment techniques that demonstrate amenability to low-intensity delivery and are evidence-based [18–21]. PM+ is delivered over 5 weekly sessions of 90 min duration. Clients are systematically taught four strategies: (1) stress management; (2) problem solving; (3) behavioral activation and (4) skills to strengthen social support. The PM+ program is being made available in different formats. In the current RCT, the PM+ individual version will be tested.

PM+ providers will be female CHWs, who will be selected based on individual interviews. PM+ providers will meet the following criteria: (1) High school diploma (form 4 level of education or above); (2) Reasonable proficiency in both Kiswahili and English language; (3) 1-year training post-secondary school as CHWs or health related career; (4) 2-years and above experience in community work; and (5) Already working as a CHW within a given geographical area. PM+ providers will receive a total of 2 weeks of training. In addition, one professional Kenyan supervisor will be employed for each of the three health facility areas.

Protocol adherence will be ensured by the supervisors and weekly group supervisions of the CHWs [22]. Supervisors will receive weekly supervision and on-the-job training in supervision skills by the project intervention consultant ([name]).

To evaluate treatment fidelity, 10 % of all PM+ sessions will be attended by the supervisor, using a checklist to ensure basic elements of the PM+ intervention have been followed as required.

At the beginning of every PM+ session the PSYCHLOPS will be administered. This instrument, in contrast to above named instruments will be administered by the CHW to assess and monitor progress on problems for which the person seeks help.

### Enhanced treatment-as-usual (ETAU)

Treatment-as-usual in primary healthcare centers in Nairobi, Kenya to individuals with common mental disorders usually consists of no or placebo treatment. For this study, treatment as usual will be substantially enhanced. Participants in the ETAU group will be referred to their primary care clinicians (usually nurses) for follow-up. These primary care nurses will have received a 3-day training; 1 day on basic psychological first aid communication skills and building on this with training from the International Federation of Red Cross non-specific lay-counselling resource [23]. This resource focuses on ethical considerations for lay counsellors, structuring a helping conversation and referral for high care.

We will seek to keep track of the types and amount of support participants receive through the SRI. If, during this treatment or during the study’s assessments participants in ETAU arm show severe psychiatric disorders or problems (e.g., psychosis or suicidality) that require immediate specialist treatment and follow-up, they will be referred to the subcounty hospital, which has been contracted to provide gratis care to the participants referred for these problems.

### Screening measures

The WHODAS [13] is a generic assessment instrument assessing general functioning, health and disability. Simple to administer, it is applicable across all health states, including mental disorders, and across cultures. WHODAS covers six domains (cognition, mobility, self-care, getting along, life activities, and participation). It assesses difficulties people have due to their illness across these domains during the last 30 days. Difficulties are scored as none, mild, moderate, severe, or extreme. We will use the 12-item interviewer administered version. The WHODAS has been validated in Kenya.

The GHQ-12 [24, 25] assesses level of general psychological distress during screening. The GHQ-12 consists of 12 questions that are scored on a 4-point scale ranging from 0 to 3. The total GHQ-12 score is obtained by summing up the scores of the individual items and ranges between 0 and 36 with higher scores representing higher levels of distress. When used as a screening tool, the GHQ-12 is usually scored bi-modally (i.e.-0-0-1-1), and ranges between 0 and 12. In a previous study in Kenya, a cut-off of higher than 2 has been reported to indicate clinical levels of distress [26].

Data on socio-demographic information (sex, age, education, marital status and work status) will be collected through questions A1-A5 of the WHODAS.

### Primary outcomes

Primary outcomes are the level of psychological distress as measured with the GHQ-12 at 3 months follow-up (i.e., 3 months after the 5th PM+ session) and general functioning as measured with the WHODAS.

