The post-intervention assessment (WHODAS, GHQ-12, PCL-5, PSYCHLOPS) is scheduled 7 weeks after the pre-intervention assessment (i.e., 1 week after the 5th PM+ session), and the follow-up assessment (WHODAS, GHQ-12, PCL-5, LEC, PSYCHLOPS, SRI) is scheduled at 13 weeks after the post-intervention assessment (i.e. 20 weeks after inclusion, in line with the timing of the follow-up assessment for the PM+ participants). The participants who receive PM+ will also be administered the PSYCHLOPS by the non-specialist helpers at the beginning of each PM+ session. Table 1 presents an overview of measures that are administered at each of the assessments.

**Table 1 Tab1:** Overview of measures administered at the assessments

Concept	Pre-assessment measures	Post-treatment assessment measures	3-months post-treatment follow-up assessment measures
1. Psychological distress	GHQ-12 (*screener and primary outcome*)	GHQ-12	GHQ-12
2. Functioning	WHODAS (*screener*)	WHODAS	WHODAS
3. PTSD symptoms	PCL-5	PCL-5	PCL-5
4. Perceived problems	PSYCHLOPS	PSYCHLOPS	PSYCHLOPS
5. Adverse life events	LEC		LEC
6. Violence against women	WHO-VAQ		
7. Costs of care	SRI items		SRI items

All instruments will be delivered in interview format as many participants are expected to be illiterate. Female independent assessors, most holding a tertiary-level degree in psychology or a related discipline, and fluent in Kiswahili and English will carry out the screening and pre and post assessments. Assessors will have received a three-day training covering administering the instruments, common mental disorders, general interview techniques, and ethical research conduct. An additional one-day training in psychological first aid and how to support women experiencing emotional distress will also be provided for assessors. Ongoing monitoring of assessors’ competency will be conducted through regular supervision by the trial manager. The assessors will be blind to the allocation status of the participants.

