### Sample size

A total number of 494 participants will to be included. Since we are not aware of intervention studies that have been carried out in this population, and we expect the population to be heterogeneous with respect to the types of common mental disorders, we aimed for a small to medium effect size of *d* = 0.04 in GHQ-12 symptom score in the PM+ group as compared to the control group at 3 months after the conclusion of the study. These estimates are in line with the observed effectiveness of an intervention led by lay health counsellors for depressive and anxiety disorders in a study in primary care in India [15]. Power calculations suggest a minimum sample size of 133 participants per group (power = 0.95, alpha = 0.05, two-sided). Taking into account 30 % attrition at follow-up, at least 346 participants (173 per group) need to be included. Further, since we estimate that 70 % of women in this distressed sample would have a history of GBV, we intend to include at least 494 women in the study.

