### Analysis

To determine comparability between the conditions at baseline, multiple planned comparisons will be conducted for continuous variables and Chi squared tests for categorical ones.

Hierarchical linear modeling (HLM) analysis will be carried out to assess differential change over time in GHQ, WHODAS, and PSYCHLOPS scores between groups. For each outcome, the effects of time of measurement, group, and the group-by-time interaction will be analyzed. HLM presumes intent-to-treat analyses as HLM allows the number of observations to vary between participants and effectively handles missing data. Time (linear and quadratic), treatment condition, and their interaction will be included in the models. Fixed effects parameters will be tested at 95 %CI. The Level 1 model will represent within-patient change over time, and the Level 2 model will predict variation in within-patient change over time and encompass between-patient variables. Outcome analyses will be reported primarily in women reporting GBV, and secondarily for women affected by all forms of adversity.

Descriptive analyses will be carried out in SPSS and HLM analyses in Stata version 11.2. Across all analyses, two-tailed tests will be reported with *p* < 0.05.

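### The Primary outcomes section names both GHQ-12 and WHODAS, but Table 1 marks only GHQ-12 as primary, and nothing says how two primaries tested at 0.05 would be judged

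*Protocol article*

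**What the plan says.** The Primary outcomes section uses the plural and opens "Primary outcomes are the level of psychological distress as measured with the GHQ-12 at 3 months follow-up". After a parenthesis on timing it adds "and general functioning as measured with the WHODAS". No time point follows WHODAS.

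Table 1, under Procedure, attaches a role to exactly these two instruments in its pre-assessment column. GHQ-12 is "GHQ-12 (*screener and primary outcome"; WHODAS is "WHODAS (*screener". Both are measured again after treatment and at the 3-month follow-up.

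The Sample size section is written for GHQ-12 alone. It gives an "effect size of *d* = 0.04 in GHQ-12 symptom score in the PM+ group", with "power = 0.95, alpha = 0.05, two-sided".

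The Analysis section lists GHQ, WHODAS and PSYCHLOPS side by side without rank, and ends: "Across all analyses, two-tailed tests will be reported with" p < 0.05. It makes women reporting GBV the main reporting set.

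**The concern.** The primary outcome decides whether the trial has succeeded. Suppose WHODAS improves and GHQ-12 does not. Under the Primary outcomes section one of two primaries is positive; under Table 1 the only primary is negative. The article supports either account, so the choice could be made after the results are known. The Abstract and Discussion tie further roll-out, and publication of the manual, to PM+ being shown effective, so the choice has consequences.

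If two primaries are intended, a second question follows: must one or both be significant? Each answer affects a stated operating characteristic. If one suffices, 0.05 per test does not hold the overall error at 0.05. If both are needed, the power computed for GHQ-12 alone is not the power of the trial's claim.

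**Working it through.** **1. The passages side by side**

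| Place | GHQ-12 | WHODAS |
|---|---|---|
| Primary outcomes | primary, 3 months | primary, no time point of its own |
| Table 1 | screener and primary | screener |
| Sample size | basis of the calculation | not mentioned |
| Analysis | two-sided 0.05 | two-sided 0.05 |

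The direct conflict is between the first two rows. The third fits Table 1 but does not contradict the first, because a trial with two primaries may be sized on one of them.

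**2. Family-wise error if either primary suffices**

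Inputs: two two-sided tests at 0.05 (Analysis). The correlation r between the test statistics is not in the document, so a range is assumed.

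Independent case: 1 − (1 − 0.05)² = 1 − 0.9025 = 0.0975.

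Correlated case: P(|Z₁| > 1.96 or |Z₂| > 1.96) for a standard bivariate normal with correlation r.

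| r | 0 | 0.3 | 0.5 | 0.7 | 0.9 |
|---|---|---|---|---|---|
| Error | 9.75% | 9.5% | 9.1% | 8.35% | 7.0% |

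With 0.025 each, the independent case is 1 − 0.975² = 4.94%, and positive correlation lowers it. If both outcomes are required at 0.05, the error is at most 5%.

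**3. The plan's own sample size**

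The stated result is: "Power calculations suggest a minimum sample size of 133 participants per group". It does not follow from the stated inputs. By two-sided t-test at alpha 0.05:

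- d = 0.04, power 0.95: about 16,245 per group.
- d = 0.40, power 0.95: 164 per group.
- d = 0.40, power 0.90: 133 per group.

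This is a separate problem. Below I assume that d = 0.40 was meant, since the text calls the effect small to medium.

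**4. Power under each rule**

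Numbers per arm at follow-up:

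- Women with a GBV history: 247 × 0.70 (GBV history) × 0.70 (retained) = 121.
- All women: 247 × 0.70 (retained) = 173.

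Single outcome, two-sample t-test, d = 0.40:

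| n per arm | alpha 0.05 | alpha 0.025 |
|---|---|---|
| 121 | 0.87 | 0.80 |
| 173 | 0.96 | 0.93 |

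Both required at 0.05, with d = 0.40 assumed for WHODAS as well (the document gives no WHODAS effect). Normal approximation: mean of each statistic = 0.40 × √(n/2), which is 3.11 at n = 121 and 3.72 at n = 173.

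| n per arm | r = 0 | r = 0.5 | r = 0.7 |
|---|---|---|---|
| 121 | 0.77 | 0.79 | 0.81 |
| 173 | 0.92 | 0.93 | 0.94 |

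**The case against.** Table 1 is an overview of what is measured when, not an endpoint definition. The Primary outcomes section is explicit, and the Secondary outcomes section does not list WHODAS. An incomplete table label is therefore a plausible explanation. This stands as a reason not to presume that Table 1 is the correct one. It does not remove the conflict: the table does assign primary status, and gives it to only one of the two instruments.

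Three stronger readings are tempting, and the document does not support them.

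- A reader might infer that the trial has a false-positive rate near 9%. That requires a rule that either outcome suffices, and no such rule is stated. The 0.05 sentence fixes a nominal level; it does not say how two primaries combine.
- A reader might count the GHQ-12-only power calculation as a further contradiction. It is not one; it only fits the Table 1 reading.
- A reader might say that WHODAS has no time point. The 3-month visit named in the same sentence is the natural reading, and WHODAS is scheduled there. The wording is loose rather than wrong.

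Finally, a condensed article may leave the combination rule to a full protocol or analysis plan that is not shown, so silence on that rule alone would be no finding. But the two conflicting designations are in this article, and any adjustment made elsewhere would have to depart from its statement that all tests use 0.05.

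**Conclusion.** The point holds in a limited form. The article gives two incompatible designations of the primary outcome, and its uniform 0.05 level does not settle how two primaries would be judged.

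The consequences are conditional. If either outcome suffices, the family-wise error is about 8–10% for correlations from 0 to 0.7. If both are required, the error is not inflated, but power for the joint claim is below that for GHQ-12 alone: about 0.77–0.81 against 0.87 at 121 per arm. If GHQ-12 is the single primary, neither problem arises.

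The power figures assume d = 0.40, the article's own 70% GBV share and 30% attrition, and for the joint claim an equal effect on WHODAS. The correlation is an assumption throughout.

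**What to change.** Make the Primary outcomes section and Table 1 agree, and state that WHODAS is judged at the 3-month (20-week) follow-up. Then choose one of two routes.

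1. **Single primary.** Name GHQ-12 at that visit as the sole primary outcome, and test WHODAS at the same visit at 0.05 only if GHQ-12 is significant. This agrees with Table 1 and the Sample size section, holds the error at 5% across the pair, and costs GHQ-12 no power. The price is that a formal WHODAS claim becomes conditional on GHQ-12.
2. **Two primaries.** Keep both, mark WHODAS as primary in Table 1, and state either Holm or a both-required rule. Restate the power for the chosen rule. Under Holm the first step is at 0.025; for an outcome tested at that level, power falls from 0.87 to 0.80 at 121 per arm, or from 0.96 to 0.93 at 173.

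Either route is a change of wording, plus a revised power statement for the second. Under the second, the sentence applying 0.05 to all analyses must also be qualified if Holm is used. The registry entry is not shown, so whether it needs the same correction should be checked.

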### Secondary outcomes

Posttraumatic stress disorder (PTSD) symptoms will be measured using the PCL-5 [27], which is a 20-item checklist corresponding with the 20 DSM-5 PTSD symptoms. Items are rated on a 0–4 scale and add up to a total severity score of 80. The PCL-5 will be adapted to ask for symptoms in the last week (rather than month) to enhance sensitivity to change.

PSYCHLOPS [28] will be administered at all assessments and at the beginning of each PM+ session, and assesses progress on problems for which the person seeks help. It consists of four questions that encompass three domains: problems (2 questions), functioning (1 question) and wellbeing (1 question). Participants are asked to give free text responses to the problem and function domains. Responses are scored on an ordinal six-point scale producing a maximum score of 20 (5 points per question). The PSYCHLOPs version administered at posttreatment and follow-up also includes an overall valuation question (determining self-rated outcome ranging from “much better” to “much worse”). PSYCHLOPS has been validated in primary care populations across several countries.

### Other measures

Previous stressor exposure will be assessed using the LEC [29]. This is a widely used list of 17 experienced or witnessed events, such as rape, serious injury, combat exposure, or the sudden death of a loved one. A Kiswahili version of this list is available [30]. At post-test the question phrasing will be adapted to capture life events that have occurred since commencing in the trial.

Five key questions of the Swahili version of the WHO-VAW as developed for use in the WHO Multi-Country Study on Women’s Health and Domestic Violence [31] are administered.

Indicators of economic impact will be assessed using the WHODAS question on days out of role and by selected SRI [32] questions on health care service use.

### Process evaluation

The feasibility, and difficulties and successes in carrying out research and intervention activities will be explored through semi-structured interviews with 20 key informants, including 5 CHWs. The burden of completing the assessments and PM+ on the time and effort of participants, satisfaction with the intervention, and barriers and facilitators to adherence will be explored through semi-structured interviews with a sample of 5 participants (including participants that have dropped out). In addition, 5 decision-makers with responsibilities for developing or implementing health policy, including heads of the relevant clinics, and 5 PHC staff (clinical officers/nurses) will be interviewed to obtain their perceptions of the benefits and challenges of integrating PM+ into the CHWs routine service provision.

### Analysis

To determine comparability between the conditions at baseline, multiple planned comparisons will be conducted for continuous variables and Chi squared tests for categorical ones.

Hierarchical linear modeling (HLM) analysis will be carried out to assess differential change over time in GHQ, WHODAS, and PSYCHLOPS scores between groups. For each outcome, the effects of time of measurement, group, and the group-by-time interaction will be analyzed. HLM presumes intent-to-treat analyses as HLM allows the number of observations to vary between participants and effectively handles missing data. Time (linear and quadratic), treatment condition, and their interaction will be included in the models. Fixed effects parameters will be tested at 95 %CI. The Level 1 model will represent within-patient change over time, and the Level 2 model will predict variation in within-patient change over time and encompass between-patient variables. Outcome analyses will be reported primarily in women reporting GBV, and secondarily for women affected by all forms of adversity.

Descriptive analyses will be carried out in SPSS and HLM analyses in Stata version 11.2. Across all analyses, two-tailed tests will be reported with *p* < 0.05.

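### The planned model gives the pre-randomisation GHQ-12 a free mean in each arm and tests differential change: valid, but less efficient than a common or adjusted baseline

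*Protocol article*

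**What the plan says.** The Analysis section states the aim of the hierarchical linear model as to "assess differential change over time in GHQ, WHODAS, and PSYCHLOPS scores between groups". It lists the terms: "For each outcome, the effects of time of measurement, group, and the group-by-time interaction will be analyzed", and adds "Time (linear and quadratic), treatment condition, and their interaction will be included in the models". On covariates it says only that "the Level 2 model will predict variation in within-patient change over time and encompass between-patient variables". Baseline GHQ-12 is not named among these, and no common baseline mean is imposed.

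The Primary outcomes section defines the GHQ-12 outcome as a level at one time: "level of psychological distress as measured with the GHQ-12 at 3 months follow-up". The Procedure section and Table 1 give three GHQ-12 assessments: pre-assessment, week 7 and week 20. The Randomization section places randomisation after pre-assessment.

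The Sample size section aims at a "small to medium effect size of *d* = 0.04 in GHQ-12 symptom score" at 3 months and reports: "Power calculations suggest a minimum sample size of 133 participants per group". It names no test and no baseline correlation.

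**The concern.** A quadratic in time needs at least three occasions, and there are exactly three. The pre-assessment score must therefore be one of the outcome values. With a group term in the model, each arm has its own baseline mean, and the group-by-time terms measure how far the arms diverge from those separate baselines.

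Because baseline is measured before randomisation, the expected arm difference at baseline is zero. Estimating that difference, and in effect subtracting it, adds sampling noise to the treatment effect without protecting against anything. At stake is the precision of the primary comparison, which is to be reported first in women reporting GBV, a subset of those randomised.

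**Working it through.** **The plan's own figure.** With two groups, 1:1, SD 1 and two-sided alpha 0.05:

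- d = 0.04, power 0.95: about 16,244 per group.
- d = 0.40, power 0.95: 163 per group (normal approximation).
- d = 0.40, power 0.90: 132.3 per group by the two-sample t-test, rounded up to 133.

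So 133 is not reproduced by the printed inputs. It is matched by a follow-up t-test at d = 0.40 and power 0.90. That mismatch is a separate matter; here it only explains the use of d = 0.40.

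**Inputs.**

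- d = 0.40 in follow-up SD units: assumed, as above.
- Evaluable women per arm: 247 × 0.7 (share with GBV) × 0.7 (retained after 30 % attrition) = 121.
- r, the baseline to follow-up correlation: not in the article; taken as 0.3, 0.5 and 0.7.
- s = baseline SD / follow-up SD: not in the article; taken as 1 and 0.8, since entry on a GHQ-12 threshold may narrow the baseline spread.

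**Formulas.** Variance factor per woman, follow-up SD = 1, complete data:

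- difference in change: 1 + s² − 2rs, which is 2(1 − r) when s = 1
- follow-up only: 1
- baseline-adjusted: 1 − r²

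The change factor minus the adjusted factor is (s − r)². Change is therefore never more precise, and it only ties when r = s. With equal SDs the variance ratio is 2/(1 + r): 1.54, 1.33 and 1.18 at the three values of r.

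Power = Φ(0.40 × √(121/2) / √factor − 1.96), where 0.40 × √60.5 = 3.111.

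| s | r | Factor: change | Factor: adjusted | Power: change | Power: follow-up only | Power: adjusted |
|---|---|---|---|---|---|---|
| 1 | 0.3 | 1.40 | 0.91 | 0.748 | 0.875 | 0.903 |
| 1 | 0.5 | 1.00 | 0.75 | 0.875 | 0.875 | 0.949 |
| 1 | 0.7 | 0.60 | 0.51 | 0.980 | 0.875 | 0.992 |
| 0.8 | 0.3 | 1.16 | 0.91 | 0.824 | 0.875 | 0.903 |
| 0.8 | 0.5 | 0.84 | 0.75 | 0.924 | 0.875 | 0.949 |
| 0.8 | 0.7 | 0.52 | 0.51 | 0.991 | 0.875 | 0.992 |

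**Break-even against follow-up only.** Setting 1 + s² − 2rs = 1 gives r = s/2. That is 0.5 with equal SDs and 0.4 at s = 0.8, with complete data.

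**Check with the three-visit model.** The table treats the model as a two-point change score. I repeated it as a likelihood model with visits at 0, 7 and 20 weeks, compound symmetry, 173 women with GBV per arm (247 × 0.7) and 30 % missing at week 20 only. At r = 0.3:

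- s = 1: power 0.80 for change with free baselines, 0.91 with a common baseline mean.
- s = 0.8: 0.85 and 0.91.

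The completer follow-up comparison gives 0.875. With this missingness and equal SDs, the break-even falls to about r = 0.44.

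**The case against.** Group, time and group-by-time in a mixed model is a standard analysis and unbiased under randomisation. The article states nothing false here, and it leaves room for covariates at Level 2, which a full analysis plan could fill. The validity part stands: this is an efficiency point. The appeal to an analysis plan is weaker. The free group term, quadratic time and the differential-change target are written into the article, so a plan that removed the free baseline would be changing the stated model rather than completing it.

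It can also be said that no section names the primary contrast. The outcome is defined as a level at 3 months, and the same fitted model can yield the week-20 arm difference, which does not carry the change-score penalty. This is a fair reason to name the contrast. It does not remove the loss: with free baselines and complete data that difference has factor 1, still above 1 − r².

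The size is uncertain too. Entry on a GHQ-12 threshold may lower r, but the same restriction shrinks the baseline SD, which softens the loss. At r = 0.3 the gap goes from 0.75 vs 0.90 with equal SDs to 0.82 vs 0.90 at s = 0.8. This stands, and both cases must be shown.

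A reader might go further and infer that the planned analysis is weaker than the test that sized the trial, with r = 0.5 as the threshold. The article does not support that as fact. It gives neither r nor the SDs and names no test, so the sizing comparison is an inference from 133 matching a t-test under inputs other than those printed. The value 0.5 holds only with equal SDs and complete data.

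**Conclusion.** The concern holds as a loss of efficiency. The model as written lets the arms differ at a baseline that precedes randomisation, and the resulting change contrast is less precise than a baseline-adjusted or baseline-constrained one unless r happens to equal the SD ratio. Over the range examined, the cost in the GBV analysis set runs from about 15 power points (r = 0.3, equal SDs) to practically nothing (r = 0.7, s = 0.8). It rests on d = 0.40, 121 evaluable women per arm, and values of r and s that the article does not supply.

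The planned effect is not biased. Whether it is also less powerful than a plain follow-up comparison depends on r lying below s/2. The change is worth making because it is free, not because the trial would otherwise be invalid.

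**What to change.** In the Analysis section, choose one of two forms:

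1. Keep all three visits as outcomes but constrain the arms to a common baseline mean, by dropping the group main effect at baseline and keeping the group-by-time terms.
2. Model weeks 7 and 20 as the outcomes, with the baseline score as a covariate.

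In either form, name the week-20 arm difference as the primary GHQ-12 contrast, which matches the definition under Primary outcomes. Do the same for WHODAS and PSYCHLOPS, and for PCL-5 if it is analysed by the same model; the Analysis section does not list PCL-5 among the outcomes of the hierarchical model.

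The cost is a change of wording. Table 1 shows that all these baseline scores are already collected.

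### The stated two-level model has no provider level: if community health workers differ in their effect, the standard error of the PM+ contrast is too small, by an amount the protocol does not let one fix

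*Protocol article*

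**What the plan says.** The Analysis section of the protocol article describes the hierarchical model level by level. At the lower level, "The Level 1 model will represent within-patient change over time"; at the upper, "the Level 2 model will predict variation in within-patient change over time and encompass between-patient variables". On the fixed part: "Time (linear and quadratic), treatment condition, and their interaction will be included in the models". No term for provider, facility or area is named. Testing is two-tailed at 0.05, and outcomes are reported primarily in women reporting GBV.

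The section on the PM+ program describes delivery: five weekly 90-minute sessions in the individual format. "PM+ providers will be female CHWs, who will be selected based on individual interviews"; each already works as a CHW in a given area. There is one supervisor for each of the three facility areas. The number of CHWs and their caseload are not stated. ETAU women are referred to primary care clinicians, usually nurses. Randomisation is individual, 1:1, with 247 women per arm.

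The Sample size section has no allowance for clustering by provider.

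**The concern.** Randomising individuals does not prevent correlation that arises afterwards through a shared provider. With 247 women in the PM+ arm and CHWs recruited within three areas, it is hard to see how a CHW would treat only one woman. If some CHWs get better results than others, outcomes of women with the same CHW move together. The PM+ mean is then less precise than a model with only women and occasions assumes.

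At stake are the width of the confidence interval, the false-positive rate and the planned power. The authors chose a hierarchical model and named its levels, so the missing provider level is part of the stated analysis and not merely a detail left for later. The identifier is also hard to recover if it is not recorded while the trial runs.

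**Working it through.** **Inputs from the protocol article.** 247 randomised per arm; 30% attrition; 70% with a GBV history; two-sided alpha 0.05.

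**Assumed inputs.** 10 to 40 CHWs, equal caseloads, provider ICC (ρ) from 0 to 0.10, and d = 0.4. The article gives none of the first three. It prints d as 0.04 but calls it small to medium, which fits 0.4.

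**The plan's own figure first.** The Sample size section says: "Power calculations suggest a minimum sample size of 133 participants per group (power = 0.95, alpha = 0.05, two-sided").
- At d = 0.4, n = 2 × ((1.960 + 1.645)/0.4)² = 162.4, so 163 per group, not 133. At 133 per group, power is 0.90.
- The 346 comes from 133 × 1.3 = 173 per group, and 494 from 346/0.7.
- None of these steps contains a design effect.

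The mismatch at 133 is a separate matter. It is shown because it fixes the correct baseline for power below.

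**Analysed women with GBV per arm.** 247 × 0.7 × 0.7 = 121.

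**Formulas** (clustering in the PM+ arm only, m = 121/number of CHWs):
- Design effect in PM+: DEFF = 1 + (m − 1)ρ; in ETAU it is 1.
- True variance over model variance of the contrast: V = (1 + DEFF)/2; the true SE is √V times the model SE.
- Actual type I error: 2 × (1 − Φ(1.96/√V)).
- Power with the correct SE: Φ(0.4/√((1 + DEFF)/121) − 1.96).

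**One case in full.** 10 CHWs, ρ = 0.05: m = 12.1; DEFF = 1 + 11.1 × 0.05 = 1.555; V = 1.278; √V = 1.130; type I error = 2 × (1 − Φ(1.734)) = 0.083. Power = Φ(0.4/0.1453 − 1.96) = Φ(0.793) = 0.786.

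**Type I error, GBV women, about 121 per arm**

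| CHWs | Women per CHW | ICC 0.01 | ICC 0.02 | ICC 0.05 | ICC 0.10 |
|---|---|---|---|---|---|
| 10 | 12.1 | 0.056 | 0.063 | 0.083 | 0.116 |
| 20 | 6.1 | 0.053 | 0.056 | 0.065 | 0.080 |
| 30 | 4.0 | 0.052 | 0.054 | 0.059 | 0.068 |
| 40 | 3.0 | 0.051 | 0.052 | 0.056 | 0.062 |

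At ICC 0 every cell is 0.05.

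**Check by simulation.** 10,000 trials per setting, a t test on a change score with a CHW effect in PM+ only, 121 per arm. With 10 CHWs the rejection rate is 0.081 at ICC 0.05 and 0.118 at ICC 0.10; with 20 CHWs it is 0.065 and 0.085. These agree with the table.

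**All women, 247 × 0.7 = 173 analysed per arm.** Caseloads are larger, so the effect is too: with 10 CHWs, 0.099 at ICC 0.05 and 0.146 at ICC 0.10; with 40 CHWs, 0.060 and 0.070.

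**Power at d = 0.4, GBV women.** No clustering: 0.875. At ICC 0.05: 0.834 with 20 CHWs (about 6 women each) and 0.786 with 10 CHWs (about 12 each). The loss is 0.875 − 0.834 = 0.041 to 0.875 − 0.786 = 0.089, or about 4 to 9 percentage points.

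**The case against.** The strongest reply is that everything here is conditional. The article gives neither the number of CHWs nor an ICC, and with 30 to 40 CHWs and an ICC up to 0.05 the type I error in the GBV set is only 0.052–0.059. That stands. A reader might infer that the type I error of this trial does exceed 0.05; the document supports only that it would if CHWs differ in their effect.

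A related point also stands. If PM+ did nothing for any woman and CHWs had no influence of their own, there would be no provider variance and the test would keep its level. The tabulated figures apply when CHW effects differ but average to zero. Read as non-coverage of the 95% confidence interval for the average effect over such CHWs, the same figures also apply when PM+ works.

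Three supporting arguments that might be offered do not hold:
- **Shared area.** Women are randomised individually, so differences between areas occur in both arms and largely cancel in the contrast. Only variation between providers in their effect counts.
- **Supervision and fidelity checks.** These do not show that delivery varies. The article gives their purpose as protocol adherence and evaluating fidelity, and together with two weeks of training they would tend to reduce provider variation.
- **Clustering in the PM+ arm only.** This is right for CHWs, but ETAU women are referred to nurses and may share providers too. That would add to the problem: in a simulation with 173 per arm, 20 providers in each arm and ICC 0.05, the rejection rate is 0.100, against 0.076 with clustering in PM+ only.

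One can also treat the trial's CHWs as fixed, with inference limited to them, since the stated aim concerns the locally adapted version in Nairobi. But the article ties roll-out elsewhere to a positive result, and that looks beyond these particular CHWs.

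Finally, an analysis plan not shown might add a provider term. The article does not rule one out, but it names both levels and the fixed terms, and provider is not among them.

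**Conclusion.** The point holds in conditional form. The stated model has no provider level, while the delivery design very likely places several PM+ women with each CHW. For any positive provider ICC with more than one analysed woman per CHW, the standard error is too small; the direction is clear and the size is not. Over the assumed range in the GBV set, the true SE is 1.005 to 1.247 times the model SE and type I error runs from 0.051 to 0.116. It is negligible with many CHWs and a low ICC, and material with about 10 CHWs and an ICC of 0.05 or more.

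It would be wrong to set 0.79 beside the stated power of 0.95 and blame clustering for the gap. The baseline for 121 per arm at d = 0.4 is already 0.875 without clustering, for reasons that belong to the sample-size calculation. Clustering at ICC 0.05 with 6 to 12 women per CHW accounts for about 4 to 9 points.

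**What to change.** - Record the CHW identifier for every PM+ woman, and the nurse or facility for ETAU women where data allow.
- Fit a partially nested model: a CHW random effect in the PM+ arm, and a nurse or facility effect in ETAU where recorded; otherwise treat ETAU women as singletons. Use a small-sample correction to the degrees of freedom, because the number of CHWs may be small.
- Include area as a fixed effect, so that differences between areas, which both arms share, are not counted as CHW variance.
- State the planned number of CHWs and an assumed ICC, and report the estimated provider ICC with the results.

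The cost is one extra recorded variable, one extra variance term and slightly wider intervals. If the ICC proves close to zero, little is lost.
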